## 6.4 Withdrawal of individual participants

Participants can leave the study at any time for any reason if they wish to do so without any consequences. The investigators can decide to withdraw a participant from the study for urgent medical reasons. After withdrawal of a participant, they will be replaced if this is still compatible with the study guidelines

## 6.5 Follow-up of participants after withdrawal

After possible withdrawal, no follow-up of participants will take place. In case of withdrawal due to medical complications, participants will be referred to a general physician.

## 6.6 Premature termination of the study

The procedures for premature termination of the study can be found in the adverse events protocol of the division Human Nutrition of Wageningen University.

# SAFETY REPORTING

## 7.1 Section 10 WMO event

When it appears that the disadvantages of participation may be significant greater than was foreseen in the research protocol, participants and the reviewing accredited METC will be informed according to section 10, subsection 1, of the WMO.

## 7.2 Adverse and serious adverse events

Adverse events (AE) are defined as any undesirable experience occurring to a participant during a clinical trial, whether or not considered related to the investigation. All AE reported by the participant or observed by the investigators will be recorded.

A serious adverse event (SAE) is any untoward medical occurrence or effect that at any dose results in death:

- Is life threatening (at the time of the event)
- Requires hospitalization or prolongation of hospitalization.
- Results in persistent or significant disabilities or incapacity
- Is a congenital anomaly
- Is a new event of the trial likely to affect the safety of the participants, such as an unexpected outcome of an adverse reaction, lack of efficacy of an IMP used for the treatment of a life threatening disease, major safety finding from a newly completed animal study, etc.

All SAE will be reported to the accredited METC that approved the protocol, according to the requirements of that METC.

## 7.3 Follow-up of adverse events

All AE will be followed until they have abated, or a stable situation has been reached. Depending on the event, follow-up may require additional test or medical procedures as indicated, and/or referral to the general physician or a medical specialist.

# STATISTICAL ANALYSIS

In this cross-over study, each subject will consume the three shakes and can be used as its own reference.

Analysis of PBMC whole genome expression data will be performed using a Bayesian linear regression model (implemented in the software package LIMMA; [www.bioconductor.org](http://www.bioconductor.org/)). Raw microarray data will be normalized using RMA quantile normalization. Statistically significant changed genes will be identified by student paired t-test followed by a false discovery rate correction (FDR) The latter is used to correct for multiple testing.

Analysis of secondary and tertiary outcome variables (endothelial function, glucose etc.) will be in SPSS version 15.0. Effects of treatment (SFA, MUFA, PUFA) within each risk group (lean healthy, obese, type 2 diabetic) will be tested by repeated measures ANOVA (mixed model) using pre-defined contrasts, i.e. 2 versus 0 hrs and 4 versus 2 hrs. Additionally, incremental areas under the curve will be calculated for all significant altered outcome variables using the trapezoïdal rule and compared between treatments using one-way ANOVA.

Differences between risk groups for each treatment will be tested by one-way ANOVA followed by LSD correction. Additionally, incremental areas under the curve will be calculated for all significant altered outcome variables and compared between risk groups using one-way ANOVA.

An empty ANOVA table providing more information about the analysis is included below.

| Variable | df |
| --- | --- |
| Risk profile (diabetic, obese, control) | 2 |
| Treatment (SFA, MUFA, PUFA) | 2 |
| Time (0,2,4) | 2 |
| Interaction | 8 |
| Error | 579 |

MRI scans will be analyzed using the HIPPO tool (14). Image files will be loaded into the HIPPO software and are then analyzed using the segment slice function. This software function initiates the automatic segmentation of the abdominal image into fat and non-fat components by designating each pixel as fat or non-fat. HIPPO is based on the fuzzy c-mean approach (i.e., fuzzy logic) and is able to make unsupervised classification of data into a number of clusters by identifying different tissues in an image without the use of an explicit threshold. HIPPO then automatically divides the pixels into light (fat) and dark (non-fat) and expresses them as a twin-peak histogram. The area under the peak representing fat will be expressed as a volume (centimeters cubed). The output result will be in the form of a computer spreadsheet.

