**Study outcome:**

The main study outcome is change in PBMC whole genome expression. Secondary study outcomes are changes in inflammatory response capacity and endothelial function. Other study outcomes are plasma lipid profiles, plasma glucose and insulin values and monocyte and lymphocyte whole genome expression.

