# OBJECTIVES

The objectives are formulated to elucidate the effects of the different fatty acids in the high fat loads on gene expression of PBMC in type 2 diabetic subjects compared to healthy obese and healthy lean subjects. The main objective of this study is to elucidate whether the high fat loads (containing either SFA, MUFA or PUFA) will have different effects on PBMC gene expression in the three risk groups of subjects. Secondary objectives are to elucidate the effects of the fat loads in the different risk groups on inflammatory response capacity and endothelial function. Tertiary objectives are to investigate the effect of these fat loads in these subjects on plasma lipid profiles, glucose and insulin and monocyte and lymphocyte gene expression profiles. For more comprehensive phenotyping of the subjects we will also measure body composition, bodyfat distribution and fecal micro flora.

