## 2.1 Research questions and hypotheses

1. Can intake of high fat loads with different fatty acids (SFA, MUFA, PUFA) result in differential changes in **PBMC gene expression** in the different groups of subjects?

 *The PBMC gene expression profiles of the high risk subjects will be more affected compared to gene expression profiles of the healthy subjects.*

2. Can the **PBMC inflammatory response capacity** be influenced by fatty acid intake and will these changes be different for the high risk subjects?

* Obese and type 2 diabetic subjects will have an impaired inflammatory response capacity. The different fatty acids will differently influence this inflammatory response capacity*

3. Can intake of high fat loads with different fatty acids result in differential changes in **endothelial function** and will these changes be different for the high risk subjects?

 *The different fatty acid compositions of the shakes will result in different changes in endothelial function. The high fat load will result in a higher degree of endothelial dysfunction in the high-risk subjects compared to the healthy subjects.*

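### The significance rule stated for PBMC genes is a within-subject paired t-test, so the main objective's comparison between risk groups has no stated test

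*Protocol*

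**What the plan says.** Section 2 (Objectives) states the main objective as "whether the high fat loads (containing either SFA, MUFA or PUFA) will have different effects on PBMC gene expression in the three risk groups". Hypothesis 1 in section 2.1 is also a comparison between groups: "The PBMC gene expression profiles of the high risk subjects will be more affected compared to gene expression profiles of the healthy subjects". The Summary words the main objective more loosely, as the acute effects of the three fats on PBMC expression in obese and in diabetic obese men, and gives the outcome thus: "The main study outcome is change in PBMC whole genome expression".

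Section 8 opens by noting that each man takes all three shakes and serves as his own reference. For the primary outcome it continues: "Analysis of PBMC whole genome expression data will be performed using a Bayesian linear regression model", implemented in LIMMA. After a sentence on normalisation comes the significance rule: "Statistically significant changed genes will be identified by student paired t-test followed by a false discovery rate correction (FDR". No group term, interaction or between-group contrast is given for the gene data.

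The next paragraph changes subject: "Analysis of secondary and tertiary outcome variables (endothelial function, glucose etc.) will be in SPSS version 15.0". The between-group test appears in the text that follows: "Differences between risk groups for each treatment will be tested by one-way ANOVA followed by LSD correction". An empty ANOVA table closes that text, with rows for risk profile, treatment, time, an interaction on 8 df and error on 579 df.

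**The concern.** The risk groups are three separate sets of 22 men (section 3.1). A paired t-test needs two values from the same man, so no choice of pair makes it a comparison between groups. The secondary and tertiary outcomes receive a between-group test, while the primary outcome, for which the group question is the main objective, receives none.

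At stake is how the main question would be answered if section 8 were followed as written. The rule yields, for each risk group, a set of genes declared changed. A gene that is significant in diabetic men and not in lean men has not been shown to respond differently in the two groups. At this sample size, such splits can be common when the true response is the same.

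**Working it through.** **1. The plan's own figures.** Section 4.5 proposes 20 men per group and enrols 22 to allow for 10% dropout: 20 × 1.10 = 22 (20 / 0.90 = 22.2 would round up to 23, a trivial difference). The ANOVA table also reproduces: 66 men × 3 shakes × 3 times = 594 values, and 594 − 1 − 2 − 2 − 2 − 8 = 579. The 8 df equal 2 × 2 × 2, that is, risk group × treatment × time. Neither figure supplies a test for the genes. The table follows the SPSS text and is not tied to the expression data.

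**2. What each stated method can test.**

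| Question | Paired t-test (primary outcome) | One-way ANOVA (secondary/tertiary text) |
|---|---|---|
| Change over time within a group | yes | not needed |
| Shake against shake within a group | yes, same men | not needed |
| Group against group, per shake | no | yes, but not assigned to genes |
| Group-by-shake difference | no | no |

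The last two rows are what section 2 and hypothesis 1 ask about.

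**3. Why separate within-group results do not fill the gap.** The protocol gives no effect size, SD, power or FDR level, so these inputs are assumptions: n = 20 per group (section 4.5), two-sided p<0.001 per gene, and a true change of d SDs of the paired change, identical in every group. Power within a group is p = P(|T| > 3.883), where T is noncentral t with 19 df and noncentrality d√20. Two independent groups disagree on significance with probability 2p(1 − p); three fail to agree with probability 1 − p³ − (1 − p)³.

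| d | p | two groups disagree | three groups not all alike |
|---|---|---|---|
| 0.3 | 0.017 | 3% | 5% |
| 0.5 | 0.087 | 16% | 24% |
| 0.7 | 0.277 | 40% | 60% |
| 0.9 | 0.566 | 49% | 74% |
| 1.1 | 0.822 | 29% | 44% |
| 1.3 | 0.953 | 9% | 14% |

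For example, at d = 0.9: 2 × 0.566 × 0.434 = 0.49.

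**4. The same check under an FDR rule.** Simulation with assumed inputs: 18,000 independent genes, 1,000 of them truly changed by 0.8 SD in all three groups, 20 men per group, Benjamini-Hochberg at 5%, mean of five runs. The three paired lists held about 467 to 500 genes each. About 826 genes were significant in only one or two groups, and about 93 in all three. A direct FDR-corrected test of group difference in change flagged 0. Over four settings (1,000 or 2,000 changed genes, changes of 0.6 to 1.0 SD), 577 to 1,603 genes were significant in only some groups, and the direct test flagged 0 in each.

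**5. What the sample size basis covers.** Section 4.5 rests on around 500 genes found changed in one earlier group of 21 healthy young men, which is a within-group count. At p<0.001 a within-group change of 0.9 SD has power 0.57 with n = 20. A difference of 0.9 SD between two groups of 20 has noncentrality 0.9 × √(20/2) = 2.85 on 38 df with critical value 3.566, giving power 0.26.

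**The case against.** The strongest reply is that section 8 does name a LIMMA linear model. Such a model can carry group and interaction contrasts, nothing in the text excludes them, and contrast matrices are commonly left to an analysis plan that is not shown here. Naming both LIMMA and a Student test may also be loose wording for LIMMA's moderated paired t. Much of this stands: the software is suitable, and the two test names need only clarification. It does not remove the point, because the protocol does not leave the test open. It fixes a significance rule for the primary outcome, that rule cannot address the group question, and an analysis plan that followed it would carry the gap forward.

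A second reply is that the Summary's wording of the main objective, and the outcome as change in expression, are served by a within-subject test. That is correct. The mismatch is with section 2 and hypothesis 1, and the within-group results keep a proper use.

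Four stronger readings are tempting, and the protocol does not support them:

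- A reader might infer that the paired test cannot compare shakes. It can, since each man drinks all three, although the text does not say which pairs are meant.
- A reader might infer that the protocol plans to compare gene lists across groups. It nowhere says so. It merely states no other route to a group conclusion for genes.
- A reader might infer that a fasting or low-fat visit is needed to remove time-of-day and fasting effects. For the comparisons in section 2 it is not: between-shake contrasts cancel such effects within a man, and between-group differences in change cancel whatever is common to the groups.
- A reader might multiply the disagreement rates by the protocol's 500 genes. That figure counts genes detected as changed, not true responders, so the product would not estimate anything in this trial.

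**Conclusion.** The point holds in a limited form. As written, section 8 gives the primary outcome a test that is adequate for within-group change and for shake comparisons within a group. It gives no test of the group or group-by-shake difference that section 2 and hypothesis 1 put first. This is a conflict between the stated test and the stated objective, and it bears on the primary conclusion.

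The size is illustrative. With n = 20, p<0.001 and identical true effects, two groups disagree for about 3% to 49% of truly changed genes over 0.3 to 1.3 SD. The peak lies near 0.9 SD and the rate falls away on both sides. The cut-off, effect sizes, gene numbers and independence between genes are assumptions. The logical gap depends on none of them.

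**What to change.** In section 8, replace the paired-t sentence with LIMMA moderated-t contrasts, FDR-corrected at a stated level, on each man's change from T=0 (2 h and 4 h), with subject as block. Treat the block as random or correlated: with changes as the response, a fixed subject term would absorb the between-group difference. Name three sets of contrasts:

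- between risk groups, for each shake;
- the group-by-shake interaction;
- between shakes, within each risk group.

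Keep the within-group lists of changed genes as the answer to the Summary's wording of the objective, and state that they are not evidence of a difference between groups. In section 4.5, add that the basis of around 500 genes concerns within-group change only.

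The cost is protocol wording and a different design matrix in software already named, with no new data or visits. The downside is that fewer genes are likely to reach significance for the between-group contrasts than in the within-group lists, which may leave less material for pathway analysis of group differences.

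### Section 8 tests shake effects within each risk group in its text but tabulates one model over all 66 men, and neither names the pooled shake-by-time test that hypothesis 3 (arguably also hypothesis 2) needs

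*Protocol*

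**What the plan says.** Protocol section 8 (Statistical Analysis) describes the analysis of the secondary and tertiary outcomes in two ways.

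- **Text.** "Effects of treatment (SFA, MUFA, PUFA) within each risk group (lean healthy, obese, type 2 diabetic) will be tested by repeated measures ANOVA", in a mixed model, "using pre-defined contrasts, i.e. 2 versus 0 hrs and 4 versus 2 hrs". For outcomes found significantly altered, incremental areas under the curve are then "compared between treatments using one-way ANOVA"; the text does not say whether groups are pooled for this. Risk groups are compared one shake at a time: "Differences between risk groups for each treatment will be tested by one-way ANOVA followed by LSD correction".
- **Table.** An empty ANOVA table, offered as further detail on the analysis, has the rows "Risk profile (diabetic, obese, control) | 2" and "Treatment (SFA, MUFA, PUFA) | 2", time with 2 df, one unlabelled interaction row with 8 df, and error with 579 df.

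Section 2.1 gives the hypotheses. Hypothesis 3 includes "The different fatty acid compositions of the shakes will result in different changes in endothelial function". Hypothesis 2 includes "The different fatty acids will differently influence this inflammatory response capacity". In both questions, whether high-risk men differ is a further clause.

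Every man takes all three shakes (sections 3.1 and 8). Section 3.1 plans 22 men per risk group. Section 4.5 aims for 20 per group and adds 10% for dropout.

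**The concern.** The shake comparison is made within each man, so all 66 men can contribute to it. A test confined to one risk group uses a third of them, and its standard error is larger by a factor of sqrt(66/22) = 1.73.

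The text and the table differ on which men enter the shake test, and neither clearly supplies the test that the shake hypothesis needs. That hypothesis concerns change after the shake, so it is a shake-by-time question. The treatment main effect in the table averages over 0, 2 and 4 hours. The 0-hour sample is drawn 20 minutes before the shake (section 6.3.4), so that row dilutes the response. The interaction row is not labelled.

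Two things are at stake. The first is precision on the shake part of the hypotheses. The second is interpretation: three separate verdicts on small groups can differ by chance, and a significant result in one group beside a non-significant one in another is easily read as a difference between risk groups.

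**Working it through.** **1. Which men are in the table.** Observations: 66 men x 3 shakes x 3 times = 594. Subtract 1 for the mean, 2 + 2 + 2 for the main effects and 8 for the interaction row: 594 - 15 = 579. This reproduces the stated error df exactly. One risk group gives 22 x 9 = 198 observations, so 579 is possible only with all 66 men in one model.

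**2. What the interaction row can be.** With three factors of 2 df each, the three two-way interactions have 4 df each and the three-way has 2 x 2 x 2 = 8 df, 20 in all. A single row of 8 df matches the three-way term alone, or any two of the two-way terms. The table does not say which, so a pooled shake-by-time test is not identified.

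**3. Whether the table keeps the within-man structure.** The 579 leaves no term for man. A full factorial (27 df including the mean) with man nested in risk group (66 - 3 = 63 df) would leave 594 - 27 - 63 = 504.

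**4. Power, split against pooled.** The protocol gives no alpha, SD or effect size for these outcomes, so these are assumptions: two-sided 5%; 20 completers per group (section 4.5); one response value per man per shake, such as the 2-versus-0-hour change; one shake differing from the other two by d_z within-man SDs of the difference; equal correlation between shakes. Then ncp = n x d_z² x 4/3. The 2-df shake test has error df 19 x 2 = 38 within one group and 57 x 2 = 114 pooled with risk group in the model.

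| d_z | ncp, n = 20 | Power, one group | ncp, n = 60 | Power, pooled |
|---|---|---|---|---|
| 0.3 | 2.40 | 25% | 7.20 | 66% |
| 0.4 | 4.27 | 41% | 12.80 | 90% |
| 0.5 | 6.67 | 60% | 20.00 | 98% |

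A separate check with a paired contrast of two shakes gives the smallest d_z detectable with 80% power: 0.63 with 22 men and 0.35 with 66.

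**5. Mixed verdicts.** The three groups contain different men, so the tests are independent. If the true effect is the same in all groups and each test has power p, the chance that one or two of the three are significant is 1 - p³ - (1 - p)³.

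| d_z | p | Mixed verdict |
|---|---|---|
| 0.2 | 0.132 | 34% |
| 0.3 | 0.246 | 56% |
| 0.4 | 0.410 | 73% |
| 0.5 | 0.596 | 72% |
| 0.7 | 0.885 | 31% |
| 0.8 | 0.954 | 13% |

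The maximum possible is 75%, at p = 0.5.

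**The case against.** The strongest reply is that the plan does not confine the shake test to single groups. The table is presented as part of the analysis, it has a treatment row over all men, and its 8-df row may be the shake-by-time-by-group test. The text can also be read as asking for group-specific effects estimated within that pooled model, since it never says that three models are fitted, and the comparison of areas under the curve may be pooled. This stands in part: a reader might infer that shake effects are tested only within groups and that two thirds of the men are lost, and the document does not establish that. It does not remove the conflict, because the text and the table still point to different analyses and the pooled shake-by-time test is named in neither.

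Second, effects within risk groups are a stated aim (sections 1.2 and 2), and the study is sized per group (section 4.5). This stands. It rules out simply dropping the within-group results.

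Third, a reader might infer that both hypotheses assert a shake effect for all men. Hypothesis 3 has a free-standing shake sentence that names no group. In hypothesis 2 the shake sentence follows one about obese and diabetic men and may refer back to them, so that case is only arguable.

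Fourth, risk groups are compared directly for each shake, so group claims need not rest on comparing verdicts. True, but those comparisons take one shake at a time and do not test whether the difference between shakes varies by group.

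Fifth, a reader might infer that three tests at 5% raise the error rate to 1 - 0.95³ = 14.3%. That counts as inflation only if significance in any one group were taken to prove a single overall hypothesis, which the protocol does not say.

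Finally, the statistical analysis plan is not shown and may settle the model. That does not cure two conflicting descriptions within the protocol itself.

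**Conclusion.** The point holds as an inconsistency with a missing test: the text specifies within-group shake tests, the table specifies one model over 66 men, and a pooled test of the shake difference in response is named in neither.

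The power loss in the table above applies if the text is followed literally. It rests on the assumed alpha, completers and effect sizes. The claim that three within-group tests would usually disagree holds only for d_z of about 0.3 to 0.5 with identical effects in every group. Outside that range mixed verdicts are less common, and the protocol itself expects stronger responses in high-risk men. Only secondary and tertiary outcomes are concerned. The correction is worth making because it is specific and needs no new data.

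**What to change.** Make the text and the table in section 8 describe the same analysis:

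- Specify one mixed model over all 66 men with risk group, shake, time and all their interactions, and with man and man-by-day as random effects. Rewrite the ANOVA table to match, labelling each interaction row.
- Test shake by time, pooled over risk groups, for the shake part of hypothesis 3 and, if so intended, hypothesis 2. The planned 2-versus-0 and 4-versus-2-hour contrasts fit within this.
- Test shake by time by risk group for whether the difference in response between shakes varies by group.
- Keep the within-group shake effects as estimates with confidence intervals from the same model.

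The cost is a change of wording, with no extra men or measurements. The one drawback is that a pooled mean can hide opposite effects in different groups; the three-way test and the within-group estimates would show them. Replacing the within-group results outright would be a trade-off against a stated objective and is not proposed.

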**Nature and extent of the burden and risks associated with participation, benefit and group relatedness:**

During a screening visit 3 ml blood will be drawn and urine will be collected after a overnight fast and body weight, length, waist and blood pressure will be measured. An oral glucose tolerance test will be performed. A general and medical questionnaire will be used.

During the study period of 8 weeks each participant will visit the university on 3 mornings, separated by at least one week, and will consume within 15 minutes a milkshake containing 95 grams of fat. Blood will be collected and endothelial function will be measured both before consuming the milkshakes (baseline, T=0) and 2 hrs (T=2) and 4 hrs (T=4) after consumption of the shakes. Blood will be drawn by normal venopuncture. At time points 0 and 2 hrs 60 ml blood will be collected and at time point 4 hr 52 ml will be collected, bringing it to a total of 172 ml per day. Hb values of each participant will be monitored during the study to be sure that blood collection will not lead to anaemia.

Participants have to collect a small amount of faeces at one time point during the study period. The body composition of the participants will be measured in the Bod Pod. In addition, the participants will visit the radiology department of the hospital Gelderse Vallei in Ede for a MRI scan to determine their abdominal bodyfat distribution.

The time investment requested from the participants is 1 hour at the information meeting, 2.5 hours at a screening session, 3 x 4.5 hours at the intervention days and 1 hour for the MRI scan. The risks associated with venous blood drawing by venopuncture are minimal. The consumption of the milkshakes is not expected to be associated with discomfort, but could, in rare cases, have adverse effects such as a mild gastrointestinal discomfort (fishy aftertaste in case of PUFA shake, belching, flatulence or loose stools). MRI is a safe procedure, with no known health risk as long as no contraindication is met (see paragraph 9.4.3). MRI can result in a ‘coincidence’ finding. These findings should be reported and subjects will be informed about this.

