### 6.3.4 Intervention

Figure 1 shows the study design and table 3 summarizes the assessments performed during the intervention.

Before the start of each study day, the Hb value of each participant will be determined by using a hemoglobin analyzer (HemoCue 201). Participants with a Hb value below 8.4 mmol/L will not be measured and are asked to make a new appointment. If Hb values are normal (e.g. above 8.4mmol/L) the measurements can be started. At T=-20 min, macro vascular regional arterial stiffness will be assessed and blood samples (62 ml) will be drawn by normal venopuncture. At T=0, the high-fat milkshake will be consumed within 15 min. Blood will be drawn 2 hours and 4 hours after intake of the shake and macro vascular regional stiffness will be assessed at the same time points.

The participants will spend the entire study duration (4.5 hours) in a room close to the blood collection room, where they will be able to read books, watch television, video or DVDs, or relax in comfortable chairs. At the end of the study day a lunch will be offered to the participants. At the end of the three study days the diaries will be collected*.*

SFA

SFA

SFA

MUFA

MUFA

MUFA

PUFA

PUFA

PUFA

SFA

SFA

SFA

MUFA

MUFA

MUFA

PUFA

PUFA

PUFA

SFA

SFA

SFA

MUFA

MUFA

MUFA

PUFA

PUFA

PUFA

Obese, diabetic subjects

Obese, healthy subjects

Lean, healthy subjects

Study day 1

Study day 2

Study day 3

Washout >1 wk

Washout >1 wk

Study day 1

Study day 2

Study day 3

T=0,2,4 hrs:

- Blood sampling

- Endothelial function measurement

T=0,2,4 hrs:

- Blood sampling

- Endothelial function measurement

T=0,2,4 hrs:

- Blood sampling

- Endothelial function measurement

Figure 1: Design of the study

Table 3: Protocol on each study day.

| **Intervention time, after 10h overnight fast** | **-20 min**  (7.00am) | **0 hr**  (7.20am) | **2 hr**  (9.20 am) | **4 hr**  (11.20 am) |
| --- | --- | --- | --- | --- |
| Consumption of high fat shake |  | x |  |  |
| Blood sampling (ml) | x |  | x | x |
| for plasma/serum isolation | 20 ml |  | 20 ml | 20 ml |
| for PBMC isolation | 42 ml |  | 42 ml | 32 ml |
| PBMC gene expression | x |  | x | x |
| PBMC stimulation with LPS | x |  | x |  |
| Cytokine profile | x |  | x | x |
| Plasma fatty acid profile | x |  | x | x |
| Plasma insulin and glucose | x |  | x | x |
| Endothelial function | x |  | x | x |
| Leukocyte activation markers | x |  | x | x |

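### The same-day fasting value is subtracted or left as a free outcome level, never used as a covariate, so shake comparisons on secondary and tertiary outcomes are less precise than the data allow

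*Protocol*

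**What the plan says.** Section 8 of the protocol states that treatment effects within each risk group "will be tested by repeated measures ANOVA (mixed model) using pre-defined contrasts", and gives those contrasts as 2 v 0 h and 4 v 2 h. It adds that "incremental areas under the curve will be calculated for all significant altered outcome variables using the trapezoïdal rule and compared between treatments using one-way ANOVA". The ANOVA table in the same section gives Time three levels (0, 2 and 4 h) with 2 df, Treatment 2 df, Risk profile 2 df, a single line "Interaction | 8", and 579 error df. No covariate is named.

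A fasting value exists on every test day. The Summary says that measurements are made "before consuming the milkshakes (baseline, T=0) and 2 hrs (T=2) and 4 hrs (T=4) after consumption of the shakes", and section 6.3.4 places them before the drink: "At T=-20 min, macro vascular regional arterial stiffness will be assessed and blood samples (62 ml) will be drawn by normal venopuncture". Section 6.2 (Randomisation and blinding) randomises shake order within each risk group, and section 3.1 relies on at least one week between test days to rule out carry-over.

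For the primary outcome, section 8 names a LIMMA linear model and then says: "Statistically significant changed genes will be identified by student paired t-test followed by a false discovery rate correction".

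**The concern.** The fasting value on a test day cannot be affected by the shake drunk after it. With randomised order and an adequate washout, its expected value is the same for all three shakes. It is therefore a textbook covariate: it explains part of the day-to-day variation in the 2 h and 4 h values and carries no shake effect of its own.

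The plan uses it in two less efficient ways. Subtracting it fixes its slope at 1, which adds its full noise whenever the within-day correlation is below 1. Entering it as a free level of Time means that any effect averaged over time includes a measurement that no shake could have changed.

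What is at stake is precision in comparing SFA, MUFA and PUFA within risk groups of about 20 completers, which is the randomised comparison of the trial. The protocol gives no power for the secondary and tertiary outcomes, so there is no stated margin to absorb the loss.

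**Working it through.** **1. How T=0 enters the ANOVA table.** Section 3.1 gives 22 men in each of three groups.
- With T=0 as an outcome: 66 × 3 shakes × 3 times = 594 values, and 594 − 1 − (2+2+2+8) = 579. This is the printed error df.
- Without T=0: 66 × 3 × 2 = 396 values, and 396 − 1 − (2+2+1+4) = 386.

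The fasting values are therefore counted as outcome values.

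**2. What each stated comparison does with T=0.** Write y0, y2 and y4 for the three values on one test day.
- 2 v 0 h: y2 − y0, a change score.
- Net incremental area by the trapezoidal rule: (y0 + 2·y2 + y4) − 4·y0 = 2·y2 + y4 − 3·y0. This is three times a weighted post-shake mean minus y0, so it too is a change score. It is computed only for outcomes already found significantly altered.
- 4 v 2 h: y4 − y2. T=0 is absent, and a shake effect that is equal at both times cancels.
- Treatment row over 0, 2 and 4 h: the mean of three values, one of them taken before the shake. A constant effect d becomes (0 + d + d)/3 = 2d/3. A simulation at r=0.5 gave a mean estimate of 0.43 for a true effect of 0.64.

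**3. Assumptions for the size of the loss.** The protocol gives no variance or correlation. Assume variance 1 per value after removing the man's own mean, a common correlation r between times on the same day, the same shake effect at 2 h and 4 h, two shakes compared in 20 men, and two-sided alpha 0.05.

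**4. One post-shake time.** The change score has variance 2(1 − r) and the adjusted value 1 − r². The ratio is (1 + r)/2, which is 0.75 at r=0.5. If the change score has 80% power there, adjustment gives about 90%.

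**5. Mean of 2 h and 4 h.** The change score has variance 1.5(1 − r), and the adjusted mean (1 − r)(1 + 2r)/2. The ratio is (1 + 2r)/3. The effect is set so that the change score has 80% power (noncentral t, 19 df); the adjusted analysis uses 18 df.

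| r | Change variance | Adjusted variance | Ratio | Power, change | Power, adjusted |
|---|---|---|---|---|---|
| 0.25 | 1.125 | 0.5625 | 0.50 | 80% | 98% |
| 0.5 | 0.75 | 0.50 | 0.67 | 80% | 93% |
| 0.75 | 0.375 | 0.3125 | 0.83 | 80% | 86% |
| 0.9 | 0.15 | 0.14 | 0.93 | 80% | 82% |

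The gain is 18, 13, 6 and 2 percentage points. A simulation at r=0.5 gave 92% for the adjusted analysis, and type I error stayed between 0.046 and 0.057.

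**The case against.** The strongest reply is that the plan already deals with the baseline. The stated within-group tests include 2 v 0 h, and the incremental area also removes the fasting value. Both are unbiased under randomised order. Choosing covariate adjustment over change scores is a matter of efficiency, and the gain rests on a correlation that nobody has stated. All of that stands, and it is why this is an improvement and not an error.

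Three stronger readings are tempting, and the protocol does not support them.

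- **That the shake comparison as a whole is diluted by the pre-shake value.** Shrinkage to two thirds belongs to the Treatment row alone. The text never names that row as the within-group shake test, and the table pools the three risk groups whereas the text tests within each. Power figures for that row would describe a test that the plan does not clearly propose. The 8-df interaction line is ambiguous: a three-way term takes 2 × 2 × 2 = 8 df, while the full set of interactions would take 4 + 4 + 4 + 8 = 20. The table therefore does not show where a shake-by-time comparison sits. That supports a clarification and no more.
- **That T=0 must not be an outcome at all.** A repeated-measures model that keeps T=0 as a response but holds its mean equal across shakes gives essentially the covariate-adjusted result. The loss comes from leaving those means free.
- **That the gene-expression analysis is flawed in the same way.** The Summary defines the main outcome as change in expression, and section 4.5 builds the sample size on the number of genes changed after the shakes. Change from fasting is thus a target in its own right. The LIMMA design is not spelled out, so how T=0 enters there is open, not wrong.

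The reply does not cover everything. The 4 v 2 h contrast is blind to a shake effect that is equal at both times. The incremental area follows an earlier significance result, so it cannot recover what that test missed.

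**Conclusion.** The point holds as a cheap gain in precision for the secondary and tertiary outcomes that have a same-day fasting value. The planned 2 v 0 h contrast and incremental area remain valid. Against change scores at 80% power, adjustment in 20 men would give roughly 82% to 98% over r from 0.9 down to 0.25. The gain is therefore substantial at moderate correlation and negligible when fasting and post-shake values track each other closely.

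These figures assume equal variances, one common within-day correlation, the same effect at 2 h and 4 h, and equal expected fasting values across shakes. The last follows from randomised order together with the washout the protocol already relies on. The figures do not apply to gene expression under false discovery rate control, for which no power was computed.

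Separately, the Treatment row over 0, 2 and 4 h should not be reported as the shake effect.

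**What to change.** In section 8, for secondary and tertiary outcomes measured at T=0, 2 and 4 h, state that shakes are compared within each risk group on the 2 h and 4 h values, with the same-day T=0 value as covariate, testing shake and shake × time. Fit the man as a fixed block so that the covariate slope is a within-man slope. If the man is random, add his mean fasting value over the three days as a second covariate. Equivalently, keep T=0 as a response and constrain its mean to be equal across shakes. Where only one post-shake time is measured, as for LPS stimulation in Table 3, the same model applies without the time term.

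Amend the ANOVA table to match, name the interaction it lists, and say that Treatment averaged over 0, 2 and 4 h is not the shake test.

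For gene expression, keep the change-from-fasting tests. Optionally, use one common T=0 coefficient per risk group in the LIMMA model for between-shake contrasts.

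The cost is wording and a little model code, one or two df, and reliance on the washout already assumed. No extra men, visits or samples are needed.
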